### Primary and secondary outcome measures

The primary outcome measures will be forefoot pain intensity scored by the participant on an 11-point pain numerical rating scale (PI-NRS, where 0 = no pain and 10 = worst possible pain), foot function using the 5 point Foot Function Index (FFI-5pt) and foot disability using the FPDI [17,24,25]. The FFI-5pts has been translated into Dutch and validated for similar participants as an interview schedule. The FPDI has been validated for participants with foot problems but was not yet available in Dutch. Within the scope of this trial the FPDI has been translated into Dutch and will be validated according to methods proposed by Beaton et al.[26]. Secondary outcomes include social participation (Keele Assessment of Participation[27]) and Quality of Life (SF-12). Both primary and secondary outcome measures will be collected at baseline and after 3, 6, 9, and 12 months. Data on personal education and work history, shoe history and co-morbidity[28] are collected at baseline as possible effect modifiers or confounders.

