### Sample size

There are no evidence-based estimates for clinically important change in assessing forefoot pain or for clinically relevant differences between interventions for chronic foot pain. In a previous study it was estimated that a reduction of approximately two points on an 11-point pain intensity numerical rating scale represents a clinically important improvement [29]. We assume that the improvement in the podiatric treatment group will be one point larger than the improvement in the control group (a mean improvement of approximately 2 versus 1 point on the 0-11 point NRS, with an estimated standard deviation of 2.5). In this design the main question is "whether the podiatric treatment is more effective than the control treatment viz. a standardised shoe advice". Therefore we will perform a one-sided statistical test with the null hypothesis that podiatric treatment has either an equal outcome or a worse outcome as compared to standardised shoe advice, both outcomes having an equal clinical consequence [30].

In order to detect a 1 point difference in improvement between the groups after 12 months with a one-sided significance level of 0.05, and assuming a power of 0.8, an ICC between podiatrists and GPs of 0.05, a correlation of 0.50 between repeated measurements and a minimum of 5 patients per care provider, we would need complete data of 75 participants in each study group. We will enrol 2 × 100 patients to allow for a drop-out rate during follow-up of 25%. If every podiatrist will treat a minimum of 5 patients, 15 podiatrists will be needed to deliver the treatment in the entire intervention group.

In 17 practices of the Academic Network, with a total of n = 23,231 patients of 50 years or older, the diagnosis "foot problems" (ICPC 17) or free text words indicating foot problems were noted in the GP records of n = 497 patients within this age group. This incidence (21/1000) is in accordance with a previous estimate of 17/1000 [31]). We expect that about one third of all consulters presenting with foot problems have forefoot problems that meet our criteria [2,5], and assuming about 50% of these patients are eligible and willing to participate, a practice with a population of average age distribution can generate a minimum of 5 participants per year. This means that we will need to recruit at least 40 practices to participate in the trial to achieve the required number of patients.

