### Data analysis

Multilevel analysis will be used to estimate the overall effect of podiatric treatment as compared to standardised shoe advice on the three primary outcome measures (PI-NTR, FFI-5pt and FPDI). Both clustering due to participants being treated by podiatrists and clustering due to repeated measurements within the same individuals will be taken into account. Results will be adjusted for differences in baseline similarity, if these occur. The effect of interest is the treatment × time interaction [32] where the primary focus will be on the primary outcome measures at 3 and 12 months' follow-up. Differences in secondary outcome will be estimated using similar statistical methods. All data will be analysed using an intention-to-treat approach. In all cases, a significance level of 5% is pre-stipulated.

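### Three primary outcomes with focus on both 3 and 12 months are each given 5% with no order or success rule, while the trial is sized on pain at 12 months only

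*Protocol article*

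**What the plan says.** Protocol article, Primary and secondary outcome measures: "The primary outcome measures will be forefoot pain intensity scored by the participant on an 11-point pain numerical rating scale", and the same sentence goes on to list foot function (FFI-5pt) and foot disability (FPDI) with equal standing.

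Protocol article, Data analysis: the multilevel model estimates the effect of podiatric treatment "on the three primary outcome measures (PI-NTR, FFI-5pt and FPDI"; PI-NTR is evidently the pain rating scale. On timing, "the primary focus will be on the primary outcome measures at 3 and 12 months' follow-up". On the threshold, "In all cases, a significance level of 5% is pre-stipulated". That section does not say whether the 5% is one-sided or two-sided.

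Protocol article, Sample size: a single main question is posed, to be answered with a one-sided test of superiority. The calculation is "In order to detect a 1 point difference in improvement between the groups after 12 months with a one-sided significance level of 0.05", with 80% power and an SD of 2.5 points. No difference, SD or power is given for FFI-5pt, for FPDI, or for any outcome at 3 months.

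**The concern.** The two sections do not describe the same trial. Sample size describes one question, one outcome and one time point. Data analysis spreads primary status over three outcomes and two time points and gives every test the full 5%. Nothing in the article says how the results combine into an answer to the main question.

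This is more than silence that an analysis plan could fill. A flat 5% for every test is a stated rule, and an analysis plan that divided the 5% would have to contradict it.

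At stake is the trial's central claim. With up to six primary results and no order among them, the most favourable one can be put forward afterwards. Participants know their treatment and every outcome is self-reported, so no objective measure would expose a chance finding. The two time points also answer different questions, because the GP may change treatment once 3 months have passed without improvement.

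**Working it through.** **1. The plan's own figure.** Inputs from Sample size: difference 1 point, SD 2.5, one-sided 0.05, power 0.80, ICC 0.05, correlation between repeated measurements 0.50, 5 patients per provider, 25% drop-out.

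- Unadjusted: n = 2 × [2.5 × (1.645 + 0.842) / 1]² = 77.3, so 78 per group.
- Design effect: 1 + (5 − 1) × 0.05 = 1.2. Analysing change scores: 77.3 × 1.2 = 92.7, so 93.
- With baseline adjustment, factor 1 − 0.50² = 0.75: 77.3 × 0.75 × 1.2 = 69.6, so 70.
- Drop-out: 75 / 0.75 = 100, as stated.

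The stated 75 complete participants per group lies between these variants but is not reproduced exactly. That is a separate matter and does not affect this point. What matters here is that every input concerns pain at 12 months.

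**2. Number of primary tests.** Three outcomes × two time points = six, if each time point is tested. One overall or interaction test per outcome gives three.

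**3. Chance of at least one false positive when there is no effect.** For k independent tests it is 1 − (1 − α)^k:

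- One-sided 5%: 1 − 0.95⁶ = 26.5%; 1 − 0.95³ = 14.3%.
- Two-sided 5%, counting only false claims of benefit (2.5% per test): 1 − 0.975⁶ = 14.1%; 1 − 0.975³ = 7.3%.

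The tests will in fact be correlated. The article gives no correlation between outcomes, so 0.3 to 0.8 is assumed. For the two time points, the 0.50 in Sample size is used as the correlation between test statistics. The correlation between different outcomes at different times is taken as the product of the two. The chance that the largest statistic exceeds 1.645 (one-sided) or 1.960 (two-sided) was simulated with 1,000,000 draws:

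| Between-outcome correlation | Six tests, one-sided 5% | Three tests, one-sided 5% | Six tests, two-sided 5%, false benefit | Three tests, two-sided 5%, false benefit |
|---|---|---|---|---|
| All tests independent | 26.5% | 14.3% | 14.1% | 7.3% |
| 0.3 | 21.8% | 13.1% | 12.0% | 6.8% |
| 0.5 | 19.9% | 11.9% | 11.0% | 6.3% |
| 0.7 | 17.3% | 10.2% | 9.6% | 5.4% |
| 0.8 | 15.7% | 9.3% | 8.7% | 4.9% |
| 0.8, time correlation 0.7 | 14.3% | – | 8.0% | – |

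The nominal rate is 5% in the one-sided columns and 2.5% in the two-sided columns. The 14% end of the six-test range needs a time correlation of 0.7; at the stated 0.50 the lowest figure is 15.7%.

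**4. What a late correction would cost.** Bonferroni over six tests uses 0.05 / 6 = 0.0083 one-sided. With 75 per group and a design effect of 1.2, power for 1 point on pain falls from about 83% to 58% with baseline adjustment, or from about 72% to 44% for change scores. Keeping the power of the stated 75 would need 75 × [(2.394 + 0.842) / (1.645 + 0.842)]² ≈ 127 complete per group, and 127 / 0.75 gives 170 enrolled per group.

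**The case against.** The strongest reply is that the article never says one positive result out of several proves superiority. Pain, function and disability could be reported as three separate conclusions, each with its own 5% error rate, and how they combine is often settled in an analysis plan. This stands in part: the inflated figures apply only if any one positive result is taken to support the claim. But the article poses a single main question, names three outcomes to answer it, and offers no rule that would exclude that use.

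A reader might go further in four ways that the document does not support.

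- **Exactly six tests.** This is a natural reading, not a stated one. Data analysis also speaks of an overall effect, and says "The effect of interest is the treatment × time interaction [32] where the primary focus will be on the primary outcome measures". One test per outcome, with 3 and 12 months as highlighted estimates, fits the text, so the three-test figures belong beside the six-test ones.
- **One-sided throughout.** Only Sample size says one-sided, in a passage about pain. If the general 5% is two-sided, the figures for a false claim of benefit are lower, though still about two to five times the nominal 2.5%.
- **Only one comparison is powered.** Only one has a stated power calculation. Pain at 3 months would have similar power if the same difference and SD applied. Sizing a trial on one outcome is ordinary practice.
- **A positive result could rest on an unvalidated scale.** The article says the FPDI has been validated in people with foot problems; what is pending is the Dutch version: "Within the scope of this trial the FPDI has been translated into Dutch and will be validated". The Dutch FFI-5pt was "validated for similar participants as an interview schedule", while the Abstract has all outcomes self-administered. These are side issues, and the point does not depend on them.

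**Conclusion.** The point holds in this form: the article fixes 5% for every test across three unordered primary outcomes and two focal time points, without a success rule, and sizes the trial on only one of those comparisons. Error inflation is conditional on an any-one-positive use of the results, which the article neither states nor rules out. It disappears only if all outcomes must succeed or if one test is named in advance. Under every reading considered, the chance of a false claim is about twice the nominal rate or more. The exact size depends on the number of tests, their sidedness and the assumed correlations, so the ranges should be quoted together with those conditions.

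**What to change.** In the outcome and Data analysis sections:

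1. Name pain on the rating scale at 12 months, the comparison the trial is sized on, as the single primary test, at the one-sided 5% of the Sample size section.
2. Test FFI-5pt and then FPDI at 12 months in that fixed order, each only if the test before it succeeds. This keeps the chance of any false claim at or below 5%.
3. Report 3 months and the other time points with confidence intervals and no confirmatory claim.
4. Replace the general 5% sentence with one that states the sidedness and refers to this order.

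Bonferroni, Holm or an all-must-succeed rule would also control the error. The fixed sequence is preferred because it leaves the power of the sized comparison untouched.

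Cost: FFI-5pt, FPDI and the 3-month comparison lose stand-alone primary status, which narrows what the trial can claim on function and disability. No extra patients or data are needed. The change should be made before outcome data are seen.

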## Discussion

In this paper we have described the design of a randomised clinical trial to compare the effects of two common treatments for forefoot pain in older people. During the design of this trial we had to make some decisions which could potentially influence the trial results. In order to explore the effectiveness of podiatric treatment on forefoot problems, it would be optimal to compare the podiatric treatment to a placebo treatment. However, we aim to enrol patients who consult their GP with a need for care of their forefoot problem. Consequently, including a no-treatment arm would not be an option in view of ethical reasons. GPs frequently only provide lifestyle advice for foot problems including the advice to wear well-fitting shoes [14]. By implementing a standardised minimal intervention strategy by means of a shoe leaflet we will reflect usual GP care for forefoot problems and not deny the participants a treatment for their forefoot problem. Participants allocated to this control treatment may be disappointed and we therefore decided to offer partial reimbursement of the costs of new shoes. We expect that this will reduce potential contamination between the control and intervention group and enhance treatment adherence in the control group. We will investigate treatment adherence and contamination in our process evaluation, perform a per protocol analysis as a secondary analysis.

It is conceivable that wearing better fitting shoes has a positive result on both foot function and foot pain. Nevertheless, in this study we are mainly interested to see if referral to podiatric treatment provides a better outcome than merely shoe advice. A problem we cannot resolve is that all subjects will be aware of how they are being treated, either by receiving standardised shoe advice or podiatric treatment. The GPs will be instructed to stimulate adherence to treatment whenever possible. If the foot pain of participants in either group does not respond to treatment after 3 months, the GPs are instructed to proceed with providing an alternative treatment. Possible changes of treatment are thoroughly documented.

Furthermore, although the podiatrists will be requested to adhere to treatment protocol, it is evident that podiatric treatment will be carried out by different therapists. In this design a maximum of 5 or 6 patients will be treated by a single podiatrist. This reduces the possible influence of a therapist effect on the outcome of the study, although the GPs would then need to refer to more podiatrists than they normally do. A multilevel analysis method will be used to estimate the 'therapist effect' (variation in treatment effect due to differences in podiatrists). Forefoot problems are very heterogeneous, and the various problems may respond differently to treatment. Although this will be analysed, the study sample will prove too small to provide conclusive evidence on any subgroup effects.

The strength of this study is that we created the design for a pragmatic trial which will compare two treatments that are most often advised by GPs: the advice to wear well-fitting shoes and podiatric treatment. Therefore, the results will contribute to clinical decision making by primary care professionals in patients with forefoot problems and it will provide information on the potential benefits of a referral for podiatric care.
